### Primary End Point

The main end point, VAS pain ratings, requires patients to subjectively rate their pain on a plastic VAS where they move a tick mark to the desired location on a 0-10 scale [1].

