### Primary Study Parameters

Pain ratings will be collected 4 times a day with a VAS. VAS mean and SD will be reported, and box plots, histograms as well as *P* values for Kolmogorov-Smirnov tests will be evaluated for normality of distribution. A univariate, one-way repeated measures (RM) ANOVA will be conducted with factors group (live music intervention, recorded music active control, and standard care control) by time points (1, 2, 3, 4). The α significance threshold will be .05. The result of interest is the significance of the training×time point interaction, that is, whether the course of the data across time points was altered by the training type. Data are planned with 4 time points; in case of up to 2 missing time points, data will be interpolated [37]. Cases with more than 2 missing time points will be excluded from the analysis. Alternatively, if the residuals of the ANOVA are not normally distributed, a similar Kruskal-Wallis one-way ANOVA will be conducted.

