#### Power

The sample size was calculated using G*Power 3.1 [38], an industry-standard software. Below, we explain the parameters for an RM between-subjects univariate ANOVA as well as the final sample size. The calculation was based on the desired ability to detect a within-between interaction (intervention group×time point), with recommended internal settings from [39], which would effectively indicate whether the live music intervention altered the slope of outcome measurements compared to the recorded music or do-nothing control groups.

The effect size (partial η^2^=0.051, converted to f=0.2318206) was determined from a retrospective RM ANOVA with published data [1].

Alpha: As we have a single quantitative outcome measure, alpha may remain at the conventional .05 significance threshold.Power: Following recent recommendations to set power above the typical 0.8 to 0.9 and higher [40], the threshold was set at 0.9.Number of groups or measurements: The design calls for 3 groups, with 4 RM (see “Study Design” section; before treatment, after treatment, 3-hour, and 6-hour follow-up) for each participant.Nonsphericity correction: As mentioned earlier, retrospective analyses were conducted with the data published in [1]. The ANOVA conducted with that data passed the assumption of sphericity (*P*=.07); therefore, no correction (1) was entered in the G*Power calculation.Sample size: The sample size (n=327, Table 3) outputted from G*Power represents the total number of participants in a 3-group design required to achieve 0.9 power with an effect size of ~0.232-109 per group. Padding for a 10% dropout rate raises the per group n to 120, for a total N of 360.

**Table 3 table3:** G*Power sample size calculation.

Parameters			Value

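### If residuals look non-normal, the plan replaces the group×time interaction test with a one-way Kruskal-Wallis test that, as written, does not test that interaction

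*Protocol article*

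**What the plan says.** Three statements in the protocol article belong together.

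- **Primary hypothesis** (Primary Study Parameters): a repeated measures ANOVA of VAS pain, three groups by four time points. "The result of interest is the significance of the training×time point interaction", and "The α significance threshold will be .05".
- **Sample size** (Power): "The calculation was based on the desired ability to detect a within-between interaction", with power for which "the threshold was set at 0.9" and an effect size "converted to f=0.2318206".
- **Fallback** (Primary Study Parameters): "Alternatively, if the residuals of the ANOVA are not normally distributed, a similar Kruskal-Wallis one-way ANOVA will be conducted".

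On the trigger, the same section says that box plots and histograms will be inspected and that P "values for Kolmogorov-Smirnov tests will be evaluated for normality of distribution". It gives no cut-off. It also does not say which value per patient the Kruskal-Wallis test would rank: one rating, a mean or a change.

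**The concern.** The fallback is presented as the counterpart of the planned test, but the two have different hypotheses. The interaction asks whether the course of pain over the day differs between arms. It is unaffected by a constant difference in pain level. A one-way Kruskal-Wallis test asks whether the distribution of a single value differs between independent groups. Unless that value is a within-patient change, the pre-intervention rating is either mixed into the comparison or ignored.

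Two things are at stake if the switch is used. A real effect on the course of pain may be missed. A difference in pain level that existed before any music may be read as an effect of music. The second matters here because treatment goes by calendar week without randomization (Treatment Allocation), in a surgical population that the Limitations section calls heterogeneous. Which question counts as primary would also be settled after the data are seen, against an unstated criterion.

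**Working it through.** **1. The plan's own figure.** From Power and Table 3: partial η² 0.051, 3 groups, 4 measures, ε = 1, α 0.05.

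- f = √(0.051/0.949) = 0.23182
- λ = f² × N = 0.2318206² × 327 = 17.573
- df = (3−1)(4−1) = 6 and (327−3)(4−1) = 972; critical F = 2.1079
- Power from the noncentral F = 0.9008

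All match Table 3. The 327 patients (109 per group) are sized for the interaction and nothing else.

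**2. What each test does at that λ.** The document gives no VAS SD or within-patient correlation; SD 2 and correlation 0.6 are assumptions. Each effect pattern was scaled so that λ = n × Σ(interaction effects²) / [SD²(1 − correlation)] = 17.573 with n = 109. Recorded music has half the live effect in every pattern except the first. For example, live drops of 1, 0.5 and 0 give Σ = 0.34375 and λ = 109 × 0.34375 / (4 × 0.4) = 23.42. The scale factor is √(17.573/23.42) = 0.87.

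Rejection rates (simulation, normal data, no floor):

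| Pattern | Interaction F | Kruskal-Wallis, patient mean | Kruskal-Wallis, change to directly after |
|---|---|---|---|
| Interaction only, equal daily means | 0.91 | 0.045 | 0.86 |
| Live −0.87, −0.43, 0 (gone at 6 h) | 0.90 | about 0.2 | 0.88 |
| Live −0.97, −0.49, −0.24 (fading) | 0.90 | 0.36 | 0.95 |
| Live −0.83 at all three later times | 0.90 | 0.66 | 0.86 |
| Constant shift −0.8 live, −0.4 recorded, also before music (no interaction) | 0.04 | 0.88 | 0.04 |
| No difference | 0.05 | 0.05 | – |

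So Kruskal-Wallis on patient means falls short of the planned 0.90 in every interaction pattern, by an amount that depends on how far the effect moves the daily mean. It rejects most often in the one pattern that contains no interaction.

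Kruskal-Wallis on a single later rating rejects in 0.09 to 0.10 of trials in the first pattern and 0.73 to 0.74 under the constant shift. Entering all four ratings as separate rows breaks independence: the null rejection rate is about 0.31 to 0.33 instead of 0.05.

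**3. How often the switch would fire.** The scale is bounded ("they move a tick mark to the desired location on a 0-10 scale", Primary End Point), but no mean, share of zeros or residual distribution is given. For a normal VAS clipped at 0 and 10, SD 1.5 to 2.5, 109 per group, the residuals at one time point fail at P < .05 (an assumed cut-off) in:

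| Mean VAS | Lilliefors-corrected KS | Uncorrected KS |
|---|---|---|
| 2 | 85–100% | 5–100% |
| 3 | 9–97% | 0–37% |
| 4 | 7–14% | 0–1% |
| 5 | 5–9% | 0–1% |

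**4. Whether the switch protects anything.** With a floor and (mean, SD) of (2, 2), (3, 2) and (3, 2.5), the interaction F test keeps its type I error at 0.047 to 0.053. Its power for the sustained pattern is 0.83 to 0.87. In these cases there is no error inflation for the switch to cure.

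**The case against.** Three points limit the conclusion.

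**The trigger.** A reader might infer that the switch is likely to fire because VAS has a floor at 0. The document does not support that. A floor makes residuals non-normal only if many ratings lie near it, and the one diagnostic reported from the earlier data is sphericity. Nor does the document set a mechanical P < .05 rule; graphs and P values are to be looked at together. This objection stands in full: the firing rate is unknown. The cut-off itself could reasonably sit in a fuller analysis plan.

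**The test.** A reader might also infer that Kruskal-Wallis can never address the interaction. Applied to change from the pre-intervention rating it tests a contrast within the interaction, with 0.86 to 0.95 power for change to the directly-after rating in the table above, and it ignores a constant shift. This also stands. The defect is that the plan names no change score. Patient means and pooled rows are candidate readings of the sentence, and neither is what the authors say they will do; the pooled error rate in particular should not be attributed to them.

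**The weight.** The repeated measures ANOVA remains the stated primary analysis and the fallback is conditional. True, but a fallback for the only confirmatory test should still address the confirmatory hypothesis, and nothing else in the document supplies that.

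**Conclusion.** The point holds as a mismatch between the primary hypothesis and its named fallback. It does not depend on how often the fallback would be used. If it is used as written, the primary question changes.

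Under SD 2, correlation 0.6 and 109 per group, about 0.90 power for the interaction becomes roughly 0.04 to 0.20 on patient means when the effect leaves the daily mean unchanged or has gone by 6 hours. It becomes 0.36 to 0.66 when the effect lasts. A pre-existing constant shift of 0.8 and 0.4 points is declared significant in about 0.88 of trials, against 0.04 for the interaction test. These sizes rest on the assumed SD, correlation and effect patterns. The mismatch itself rests only on the text.

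**What to change.** Replace the Kruskal-Wallis sentence with one that does two things:

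1. The group×time point interaction remains the primary test whatever the normality check shows.
2. One sensitivity analysis of the same contrast that does not assume normality is prespecified. It could be a Kruskal-Wallis or other rank test on within-patient change from the pre-intervention rating, with the later rating named, or bootstrap inference for the interaction.

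The cost is one sentence and one extra analysis; no patients or data. The drawback is that a single change score captures only part of the interaction, so the choice matters. In a check with 120 per arm and live effects of −1.0, −0.5 and 0, power was 0.96 for change to the directly-after rating and 0.62 for change to the mean of the three later ratings. Bootstrapping the interaction avoids that choice. The wording should be settled before any outcome analysis, including the preliminary analysis that the Results section plans once 0.8 power is reached.

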### Secondary Study Parameters

For metrics that are collected on the same schedule as the VAS (EEG alpha power, delta/alpha power ratio, entropy metrics, HR, respiration rate, and blood pressure), the values per participant will be entered into the same *F* test described for the VAS ratings (as well as correlated with other baseline parameters as described in the “Other Parameters” section). For blood marker metrics that have 2 data collection points, a similar RM ANOVA will be conducted, but with 2 as opposed to 4 measures, and a significant interaction between treatment and time point would indicate whether treatment significantly impacted the amount of the neuroinflammatory blood marker. Categorical incidence metrics (delirium and POCD) will be evaluated with a one-way ANOVA to determine whether treatment impacted these neuroinflammatory-related complications. Delirium and signs of delirium will be perceived using the DOSS. The DOSS is a screening instrument for delirium, consisting of 13 items, and will be filled by a registered nurse during hospital admission until discharge. Nurses have frequent contact with the patients and are in a good position to observe behavior changes 24 hours a day when patients are admitted. The DOSS is already part of a routine in the surgical wards and all registered nurses are already trained. Likewise, scalar pain medication dosage will be averaged over 24-hour periods per patient and entered into a chi-square test to determine whether the dosage was significantly different across the 3 treatment groups. As this is exploratory and serves to inform future hypothesis-directed testing, we will not correct for multiple comparisons.

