Design procedures are chronologically displayed in Figure 1. Preoperative questionnaires will be collected to assess cognitive function (6-item cognitive assessment [6CIT]) [27,28] and musical background (excerpt from the Dutch Musical Background Questionnaire [DMBQ]) [29,30]. Postoperative data collection procedures per day of treatment include pain visual analog scale (VAS) ratings, heart rate (HR), and blood pressure measuring 4 times a day (before, directly after, 3-hour, and 6-hour postintervention). EEG electrodes will be applied once in the morning and 4 EEG recordings will be collected with VAS ratings, HR, and blood pressure (before, during, 3-hour, and 6-hour postintervention). A blood sample will be collected once daily and integrated with standard care as far as possible (eg, if blood is drawn as part of standard care, the sample will be collected from the same needle). A schedule of assessments may be found in Table 1. Daily dosage of pain medication as well as any incidence of delirium (delirium observation screening scale [DOSS]) [31] or POCD will be collected.

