#### Secondary Study Parameters and End Points

The secondary study parameters (Table 2) and end points are as follows: (1) objective pain metric (volume of administered pain medication); (2) respiratory rate and tidal volume; (3) HR; (4) blood pressure; (5) neuroinflammation blood markers (IL6, NGAL, CRP, and serum TPSO); (6) behavioral indicators of neuroinflammation (delirium [31] and POCD incidence); and (7) EEG markers of neuroinflammation (alpha power, delta/alpha power ratio, and entropy).

**Table 2 table2:** Secondary study parameters.

Outcome	Metric	Statistics
Objective pain measure	Pain medication dosage (ccs)	Chi-square test
Neuroinflammation, blood markers	IL6^a^, NGAL^b^, CRP^c^, and serum TPSO^d^	*F* test (RM^e^ ANOVA, pre-post)
Neuroinflammation, behavioral indication	Incidence delirium and incidence POCD^f^	*F* test (one-way ANOVA)
Neuroinflammation, EEG^g^ indication	Alpha power, alpha/delta power, and entropy	*F* test (RM ANOVA same as primary)
Neuroinflammation, physiological	HR^h^, respiration rate, and blood pressure	*F* test (RM ANOVA same as primary)

^a^IL6: interleukin-6.

^b^NGAL: neutrophil gelatinase–associated lipocalin.

^c^CRP: C-reactive protein.

^d^TPSO: translocator protein.

^e^RM: repeated measures.

^f^POCD: postoperative cognitive decline.

^g^EEG: electroencephalogram.

^h^HR: heart rate.

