#### Blood Marker Analysis

One 10-ml vial of blood will be collected per day resulting in a maximum of 5 vials of blood over 5 days. The first sample must be taken before the first assigned intervention. Blood samples will be collected together with standard care insofar as possible. Serum extracted from blood samples will be processed by the Haemoscan lab and evaluated for the presence of 4 markers associated with neuroinflammation (IL6, NGAL, CRP, and serum TPSO; see “Introduction” section).

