### Limitations

While postoperative pain is common to most patients undergoing surgical intervention in hospital, other characteristics surrounding the surgery (eg, type of surgery, duration of surgery, and underlying medical need for surgery) are widely varied across patients. Thus, a limitation of the study is that we will have a heterogeneous patient group. Considering that reduced pain VAS among patients experiencing MiMiC live music intervention compared to care-as-usual was previously a robust finding in a heterogeneous patient group [1], we do not consider our primary outcome to be affected by this heterogeneity. However, secondary outcomes related to finding neurophysiological markers of inflammation, and whether they are influenced by a music intervention, might be greatly affected by this heterogeneity. Moreover, the short duration of the intervention may further limit proper interpretation of inflammatory biomarkers, since previous studies have found neuroinflammatory biomarkers readings to be informative to overall interpretation 5 to 14 days after a medical event [43,44]. We may therefore form posthoc groups with similar surgery types when evaluating secondary outcomes, which could inform future hypotheses for further, longer term clinical research on music interventions and postsurgical neuroinflammation.

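### Blood is drawn once per treatment day, up to five samples, but the blood-marker test is fixed at two measures without saying which later sample is the second

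*Protocol article*

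**What the plan says.** Collection is described twice, consistently. Study Design states: "A blood sample will be collected once daily and integrated with standard care as far as possible". Blood Marker Analysis states: "One 10-ml vial of blood will be collected per day resulting in a maximum of 5 vials of blood over 5 days". It also fixes the starting point: "The first sample must be taken before the first assigned intervention".

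The analysis is also described twice. The statistical text under Secondary Study Parameters states: "For blood marker metrics that have 2 data collection points, a similar RM ANOVA will be conducted", using two measures in place of four. A significant treatment-by-time interaction is then to be read as an effect of treatment on the marker. Table 2 assigns a pre-post repeated measures ANOVA to IL6, NGAL, CRP and serum TPSO alike, so the two-measure description cannot be confined to some of the markers.

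Three other statements bear on timing. Under Population, patients need only one day in hospital after surgery. Under Treatment Allocation, the treatment schedule is set months ahead and patients receive whatever is running during their stay. Postoperative day is recorded, but only as one of the other study parameters.

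**The concern.** Up to five samples per patient are collected and two enter the only between-group test described for the markers. The first of the two is identifiable: it is the sample taken before the first session. The second is not. The article neither names one of samples two to five as the *post* value nor says that later samples are combined into one.

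At stake are precision and interpretability of the secondary objective, which concerns the inflammatory response to surgery. A test on two samples is less precise than one on all of them. A *post* label that is not tied to a day since surgery can also put patients at different stages of that response into the same cell.

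**Working it through.** **The plan's own figure.** The only sample-size calculation is for the pain ratings. It reproduces: λ = f²N = 0.2318206² × 327 = 17.573, with df (3−1)(4−1) = 6 and (327−3)(4−1) = 972, critical F 2.1079 and power 0.9008. It has no bearing on the blood markers, for which no power is claimed.

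**Samples drawn and tested.** Inputs: one sample per treatment day, at most five days (Blood Marker Analysis); two measures in the test (Secondary Study Parameters). Samples left over = max(0, days − 2).

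| Days treated | Drawn | Enter the test | Left over |
|---|---|---|---|
| 1 | 1 | no pair can be formed | 0 |
| 2 | 2 | 2 | 0 |
| 3 | 3 | 2 | 1 |
| 4 | 4 | 2 | 2 |
| 5 | 5 | 2 | 3 (60%) |

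The article gives no distribution of stay, so the overall share left over lies somewhere between 0 and 60%.

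**When the second value falls.** Two readings are open.
- *Post* is the last sample. It falls on treatment day 2, 3, 4 or 5, so the gap from the first sample is one to four days, depending on stay.
- *Post* is the second sample. The gap is one day for everyone. Day since surgery can still differ, because treatment starts by the calendar and not by the date of surgery.

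**Cost in precision.** Assumption: equal variances and equal correlations across days (compound symmetry). Let s² = σ²(1−ρ), with k samples per patient.

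*Constant effect on all later samples.* Variance of (mean of later samples − first) = s²(1 + 1/(k−1)).
- k = 2: 2s²
- k = 3: 1.5s², so two points cost 2/1.5 = 1.33
- k = 4: 1.33s², so 2/1.33 = 1.5
- k = 5: 1.25s², so 2/1.25 = 1.6

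*Linear trend, five-day patient.* Slope variance = s² / Σ(day − mean day)².
- All of days 1 to 5: Σ = 4+1+0+1+4 = 10, variance 0.1s²
- Days 1 and 5: Σ = 4+4 = 8, variance 0.125s², ratio 1.25
- Days 1 and 4: Σ = 4.5, variance 0.222s², ratio 2.2
- Days 1 and 3: Σ = 2, variance 0.5s², ratio 5
- Days 1 and 2: Σ = 0.5, variance 2s², ratio 20

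The loss under a trend therefore depends almost entirely on which sample is the *post* value, and the article leaves that open.

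**The case against.** Much can be said for the plan. The outcome is secondary and declared exploratory. An article condenses a fuller protocol, and the choice of the *post* sample is a detail that could sit elsewhere. This is fair, and the missing definition alone would not be a point. What stands is that the article gives two counts that do not fit, up to five and two, and an analyst following the statistical text would fit the two-point model.

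A reader might infer several stronger things that the documents do not support.

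- *That the extra vials are never used.* The Introduction also plans to relate the pain outcome to these markers, and nothing limits that to two samples. Only their absence from the treatment-by-time test is shown. The burden is also reduced: samples are taken with standard-care draws where possible.
- *That postoperative day is ignored.* The statistical section on other study parameters enters continuous baseline parameters post hoc as covariates, and its list includes postoperative days. That is a partial answer, since a covariate does not define the *post* value or make day since surgery the time axis.
- *That the music effect is confounded with length of stay.* Uneven timing biases the group comparison only if timing differs by group, which nothing in the article establishes. Otherwise it mainly adds noise.
- *That the two-point test is twenty times less precise.* This needs *post* always to be day 2, a linear trend and five samples. It cannot be combined with a one-to-four-day gap, which needs *post* to be the last sample; there the ratio is 1.25 for a five-day patient.
- *That the plan overlooks the later window for biomarkers.* The Limitations section itself reports "biomarkers readings to be informative to overall interpretation 5 to 14 days after a medical event" and links this to the short intervention. With at most five treatment days it does not favour all samples over first versus last.

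**Conclusion.** The collection and analysis sections disagree on how many blood measurements there are, and the disagreement should be resolved. As written, the group-by-time test omits up to three of five samples in patients treated for five days and no surplus sample in those treated for one or two. It leaves the second value undefined and does not address patients who have only a first sample.

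The cost for five-day patients is a variance up to 1.6 times larger under compound symmetry with a constant later effect. Under a linear trend it is 1.25 times larger if *post* is the last sample, and more if it is earlier. For shorter stays the constant-effect loss is smaller (1.5 and 1.33 for four and three samples). Since stay is not described, an average over the trial cannot be given. That the *post* value falls on different days since surgery is an inference from the stay and scheduling rules, not something the article states.

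The consequence is confined to a secondary, exploratory outcome. The primary pain analysis and the sample size do not change.

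**What to change.** Make Study Design, Table 2, Blood Marker Analysis and the statistical text on secondary parameters agree on the number of samples collected and analysed.

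Replace the two-point ANOVA by a linear mixed model on all daily samples: the first (pre-session) sample as baseline covariate, postoperative day as the time axis, group, day and group-by-day as fixed effects with a group-by-day test, and a random effect for patient. With the first sample as a covariate, a constant shift on later days appears in the group term, so group and group-by-day should be reported together. The model accepts unequal numbers of samples. Patients with only a first sample still contribute no outcome, and their number should be reported by group.

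The cost is analysis wording and slightly more analysis work; the samples and postoperative day are already planned. One limit remains: later days come only from patients with longer stays, which should be noted when the results are interpreted.

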**Methods:**

This intervention study will compare subjective postsurgical pain ratings among 3 groups: live music intervention, recorded music intervention, and standard care control. The design will take the form of an on-off nonrandomized controlled trial. Adult patients undergoing elective surgery will be invited to participate. The intervention is a daily music session of up to 30 minutes for a maximum of 5 days. The live music intervention group is visited by professional musicians once a day for 15 minutes and will be asked to interact. The recorded music active control intervention group receives 15 minutes of preselected music over headphones. The do-nothing group receives typical postsurgical care that does not include music.

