### Population (Base)

The study will include patients who have undergone elective surgery in the UMCG and are hospitalized for at least 1 day following surgery. All patients must be 18 years or older and able to make their own decisions. Patients must further be able to hear music with normal or corrected normal hearing (ie, a hearing aid).

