#### Other Study Parameters

Other study parameters used in this study are as follows: (1) comorbidities (Charlson comorbidity index) [32]; (2) complications (Clavien Dindo [33] and nurse-sensitive outcomes [34]); (3) postoperative days (T0=surgery); (4) surgery characteristics (invasiveness, etc) [20]; (5) musical background (excerpt from DMBQ) [30]; (6) age; and (7) presurgery cognitive testing [22] (eg, 6-item cognitive impairment score) [28].

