### Treatment Allocation

This study will take the form of an on-off NCT [26]. An on-off NCT takes into account real-world setting limitations of certain intervention types and allocates participant inclusion by alternation. The main reason for this is that MiMiC is a well-researched intervention, whose practical implementation is not suited for randomly selected participants to not participate. On the one hand, musicians will visit the nurses’ station and play music in various rooms around the ward; thus, it is not possible to prevent participants who may be allocated non-MiMiC treatment from hearing the live music. On the other hand, a central tenet of the MiMiC intervention is inclusion and participation, thus “rejecting” patients who would want to participate in music they hear on the ward, on the basis of trial group allocation, goes against the spirit of the intervention.

In contrast, the NCT relies on the randomness of who is scheduled for surgery during a given intervention week but does not exclude any patient from the activity being conducted (listening to live or recorded music). Therefore, the treatment schedule (live music intervention, recorded music active control, and standard care control) will be predetermined months in advance, and the patients included will be offered whichever treatment is occurring during their hospital stay. The patients will, however, be asked for their consent before they are informed which treatment will be offered during their surgery recovery. This will attempt to prevent patients who are initially biased for inclusion based on their affinity to music or not.

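### Analgesic dose is averaged per patient and compared across arms with no term for postoperative day, so unequal stays or starting days could bias it in either direction

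*Protocol article*

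**What the plan says.** Study Design says that the raw data are daily: "Daily dosage of pain medication as well as any incidence of delirium" will be collected. The statistical section on secondary parameters then reduces them: "scalar pain medication dosage will be averaged over 24-hour periods per patient", and the result is "entered into a chi-square test to determine whether the dosage was significantly different across the 3 treatment groups". Table 2 repeats the chi-square test for this outcome.

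Observation time is not uniform by design. Population (Base) asks only that patients be "hospitalized for at least 1 day following surgery", and the abstract sets the music sessions "for a maximum of 5 days". Under Treatment Allocation, "the patients included will be offered whichever treatment is occurring during their hospital stay".

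Postoperative day, counted from surgery, and surgery characteristics are on the list of other recorded parameters. The later statistical section on those parameters plans post hoc models that add baseline covariates or factors, type of surgery among them, to see whether they improve the model for each outcome. The secondary analyses are declared exploratory.

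**The concern.** If analgesic use changes from day to day after surgery, a per-patient mean depends on how many days enter it and which days they are. A group comparison of such means mixes the effect of treatment with the effect of observation time. Randomisation would balance observation time in expectation, apart from any effect of treatment on stay. Here arms are filled by calendar period and all surgery types are eligible, so nothing in the design ensures that stay, starting day or case mix match across arms.

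Medication dose is labelled the objective pain metric, and the Introduction names it among the measures meant to carry the pain result from subjective to objective. A difference in mean daily dose that reflects only observation time could be read as support for the pain ratings, or as evidence against them.

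This is separate from the use of a chi-square test on a scalar dose. Replacing that test with one for continuous data would leave the present problem in place.

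**Working it through.** The protocol gives no figure for analgesic dose. Its sample size concerns the pain ratings only. It reproduces (0.2318206² × 327 = 17.573; power 0.9008 on 6 and 972 df) but has no bearing here, apart from the planned 120 patients per arm.

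**Inputs from the protocol:** one average per patient, stay of at least 1 day, at most 5 intervention days, 120 per arm, α = .05.

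**Assumptions (not in the documents):** dose on day d is 100 × r^(d−1), with r from 0.6 to 1.1; the stay distributions below; coefficients of variation of 60% between and 40% within patients.

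1. *Mean over L days:* M(L) = (100/L) × Σ r^(d−1), d = 1 to L. For L = 1 to 5:
   - r = 0.8: 100, 90, 81, 74, 67
   - r = 0.7: 100, 85, 73, 63, 56
   - r = 0.6: 100, 80, 65, 54, 46
   - r = 1: 100 throughout
   - r = 1.1: rises from 100 to 122
2. *Three versus four days, identical course:* at r = 0.7, 73.0/63.3 = 1.153, or 15%. The ratio is 1.051 at r = 0.9, 1.102 at 0.8 and 1.201 at 0.6.
3. *Starting day:* at r = 0.7, two observed days starting on day 1 average (100 + 70)/2 = 85. Two days starting on day 3 average (49 + 34.3)/2 = 41.65.
4. *Whole arms:* arm mean = Σ p(L) × M(L). Take one arm with stays spread evenly over 1 to 5 days (mean 3.0), and one with weights 2 : 1.5 : 1 : 0.75 : 0.5 (mean 13.5/5.75 = 2.35). At r = 0.7 the arm means are 75.36 and 82.73, so the shorter-stay arm is 9.8% higher. The difference is +3.3% at r = 0.9, +6.6% at 0.8, +12.9% at 0.6, zero at r = 1 and −3.2% at r = 1.1.
5. *Case mix:* keep those stays and r = 0.8, but let day-1 dose rise by 10%, 20% or 30% per extra day of stay. The +6.6% becomes +0.3%, −5.3% and −10.3%. The bias vanishes and then reverses.
6. *False positives:* 120 per arm, no treatment effect, 2000 simulated trials, one arm with shorter stays. One-way ANOVA stands in for the chi-square test, which needs categories. Rejection rates at r = 0.8, 0.7 and 0.6:
   - equal stays: 4% to 5%
   - mean stay 2.35 v 3.0 days: 10%, 16%, 22%
   - mean stay 1.96 v 3.0 days: 19%, 35%, 48%
   - at r = 1, 4% to 5% whatever the stays
7. *Does aligning on day suffice?* Comparing day-1 dose alone gives 4.1% to 5.5% when dose level is unrelated to stay. With r = 0.8, mean stays of 2.35 v 3.0 days and a 20% or 30% gradient of dose with stay, it gives 20% or 34%. Adding length of stay as a factor gives 4.3% to 5.4% throughout, but stay may itself be affected by treatment. The mixed model proposed below was not simulated.

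**The case against.** **The averaging window is not stated.** That the mean runs over the whole observed stay is an inference. A fuller protocol or SAP may fix the window, and the sentence could also mean one value per 24-hour period. This stands as a caution. On the second reading, several values per patient would enter a test that still has no day term.

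**Two unproven conditions are needed.** A reader might infer that arms with shorter stays will look as if they used more analgesic. The documents do not support that. They do not say that dose falls over days or that stays differ between arms, and steps 4 and 5 show that the direction can reverse. This objection stands in full.

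**The gap may be small.** Every arm has the same 5-day window, repeated over 15 blocks. If stays were uniform on 1 to 5 days (variance 2), the standard error of a difference in mean stay is √(2 × 2/120) = 0.18 days, ignoring clustering by week. A reader might also infer that an arm using less on every day will show a higher mean. At r = 0.7, an arm using 10% less daily does show 0.9 × 1.153 = 1.038, or 3.8% more, but only if whole arms differ by 3 versus 4 days. That is more than five standard errors. It would take a real effect on stay or strong calendar confounding, and neither is documented.

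**Mitigation is planned, and dose does not stand alone.** Postoperative day is recorded and covariate models are foreseen. They are post hoc, aimed at advice for future studies, and leave the stated dose test as it is. Once days are averaged, a day-specific adjustment is no longer possible. It would be wrong to call dose the only objective support for the pain ratings: the Introduction also names respiration rate, and Pulmonary Ventilation adds tidal volume.

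**Conclusion.** The concern holds in conditional form. The stated comparison takes no account of postoperative day in a non-randomised trial where observation time can vary. If dose changes over days and arms differ in stay or starting day, the comparison can be biased in either direction. If stays and starting days match, or dose is flat, there is no bias.

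Under the assumed 20% to 40% daily fall and a 0.65-day gap in mean stay, the spurious difference is 6.6% to 12.9% and the false-positive rate 10% to 22%. Those sizes rest on the assumed decline, stay distributions and variability, and case mix can cancel or reverse them. The 15% for 3 versus 4 days illustrates two observation lengths and is not an expected difference between arms.

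The outcome is secondary and exploratory, so the trial's main conclusion is not at risk. The change is still worth making, because a better analysis can use data already planned for collection.

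**What to change.** Replace the sentence on dose with an analysis of the daily values. Fit a linear mixed model to daily dose, suitably transformed, with arm, postoperative day as a factor, arm × day, surgery type and a patient random effect. Report the arm difference by postoperative day. Surgery type is there because step 7 shows that aligning on day does not by itself remove case-mix confounding.

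A total over a fixed window is not a safe substitute unless all patients complete the window: those discharged earlier would have incomplete totals, and the article describes no dose collection after discharge.

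The cost is a rewritten sentence and a slightly more complex model for an exploratory outcome. Daily dose, postoperative day and surgery characteristics are already to be recorded. Confounding from calendar allocation will remain, and the report should say so.
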